### Diagnostic criteria

Patients were considered to have glaucoma if they presented with asymptomatic or nonspecific complaints such as headaches, frequent changes in presbyopic corrections, noticing blind spots or scotomas, or difficulty adapting to darkness and displayed at least two of the following three clinical indicators, with an open irido-corneal drainage angle confirmed on gonioscopy: (1) an IOP reading above 21 mmHg on more than one occasion, a diurnal IOP variation exceeding 8 mmHg, or an inter-eye IOP difference of more than 5 mmHg; (2) optic nerve head (ONH) changes suggestive of glaucomatous damage, including a vertical cup-to-disc ratio above 0.5, or a cup asymmetry greater than 0.2, neuroretinal rim thinning or notching, pallor, disc hemorrhages, or abnormal vessel patterns; and (3) visual field changes consistent with glaucomatous defects. In addition, a retinal nerve fiber layer (RNFL) defect extending from the ONH in a characteristic pattern, as viewed under red-free examination, supported the diagnosis.

### Settings and location

The study is conducted at the Eye Outpatient Department (OPD), [name], All India Institute of Ayurveda (AIIA), [name].

### Trial oversight committees

The trial is being coordinated at AIIA, New Delhi. The institute is the center for the overall coordination of the trial, including participant screening and enrollment logistics, oversight of data management processes, and communication with relevant regulatory authorities. The study protocol was first submitted for review to the Institutional Review Board (IRB), which assessed its ethical and scientific merit. Upon finding it suitable, the IRB granted provisional approval along with suggested revisions. After incorporating these recommendations, the revised protocol was forwarded to the Institutional Ethics Committee (IEC) for further evaluation. Following acceptance of the final modifications, the protocol received full approval for implementation. Additionally, the Department Research Committee (DRC) comprising the research guide, co-guides, advisors, and department heads monitor the trial’s conduct, oversees adherence to the protocol, addresses any protocol-related issues, and routinely assesses recruitment progress, data quality, and the need for any protocol amendments.

### Interventions

Participants are divided into two groups; details of the interventions are given in
Table 1.

**Table 1. T1:** Details of the interventions.

Group	Intervention	Route	Dose	Frequency	Duration
Group A	POAG Standard of Care (SOC) *	Topical/oral	As per AAO-PPP-G *	As required	90 days
Group B	POAG SOC	Topical/oral	As per AAO-PPP-G *	As required	90 days
	Rasayana Formulation	Oral	2.5 g	2×/day	90 days
	Shigru Pallava Eye Drops	Topical	1 drop (0.05 mL)	4×/day	90 days

* AAO-PPP-G refers to treatments recommended by the American Academy of Ophthalmology’s Preferred Practice Pattern Guidelines. g: gram, mL: milliliter, POAG: primary open angle glaucoma, SOC: standard of care.

**Shigru Pallava Eye Drops:** Each drop (0.05 mL) contains Arka (distilled aqueous extract) of Shigru (
*Moringa oleifera* Lam.). Participants instill one drop in each eye four times daily.

**Rasayana formulation:** This is a herbo-mineral combination provided as a 2.5 g dose consisting of powdered herbal ingredients and nanoparticles of minerals (
Table 2).

**Table 2. T2:** Details and composition of Rasayana Formulation.

Sr. No.	Drug	Scientific/Botanical Name		Quantity
1	*Yashada Bhasma* (YB)	Zinc (Zn) nanoparticle		60 mg
2	*Saptamrita Lauha* (SL)	*Lauha Bhasma* (Iron (Fe) nanoparticle)		250 mg (comprising 50 mg of each constituent)
		*Yashtimadhu Churna*		
		*Triphala Churna*	*Haritaki Churna* ( *Terminalia chebula* Retz.)	
			*Vibhitaki Churna* ( *Terminali bellerica* Gaertn.)	
			*Amalaki Churna* *** *(Emblica officinalis* Gaertn.)	
3	*Rasayana Churna* (RC)	*Guduchi* Churna ( *Tinospora cordifolia* Willd.)		2190 mg (comprising 730 mg of each constituent)
		*Gokshura Churna* ( *Tribulus terrestris* Linn.)		
		*Amalaki Churna* *** *(Emblica officinalis* Gaertn.)		

*
*Amalaki Churna* is a constituent of both SL and RC. Accordingly, a single 2.5 g dose of RF contains a total of 780 mg of fine
*Amalaki* powder. mg: milligram, g: gram.

### Source of plant material and reagents

Shigru leaves were obtained from the in-house herbal garden of the AIIA. All raw herbal ingredients were sourced from reputable suppliers and authenticated by a botanist at the Regional Raw Drug Repository (RRDR), AIIA, under the Department of Dravyaguna Vigyana (Ayurvedic Materia Medica and Pharmacology). Yashada Bhasma and Lauha Bhasma were procured from a GMP-certified company (Manufacturing License No.: AYU-150). Both the SP drops and the RF were manufactured at the AIIA Pharmacy following in-house Standard Operating Procedures (SOPs) based on the Ayurvedic Formulary of India (AFI) and the Ayurvedic Pharmacopoeia of India (API), under the Department of Rasa Shastra and Bhaishajya Kalpana (Ayurvedic Iatro-chemistry). No chemical reagents (e.g., solvents or laboratory kits) were used in this study.

### Comparator

Conventional standard care of POAG, adhering to the American Academy of Ophthalmology - Preferred Practice Pattern Guidelines (AAO-PPP-G) recommendations, serves as the comparator. This may include topical eye drops (prostaglandin analogs, beta-blockers, etc.) or oral medications (e.g., carbonic anhydrase inhibitors) based on clinical judgment.

### Sample size

This is an exploratory study; no prior data exists for neuroprotection as the primary outcome in POAG with Ayurveda intervention. A minimum of 50 participants will be enrolled in total, with 30 participants assigned to the intervention group and 20 participants assigned to the control group.

### Randomization

A block randomization approach with variable block sizes is adopted to maintain balanced allocation across study arms at a 2:3 ratio. The random allocation sequence was generated by a research advisor using computer-based randomization software. Once a participant is confirmed eligible by the principal investigator (PI), enrollment will be documented in the study records, and the sealed, numbered, opaque, sequential envelopes (SNOSE) will be opened. The PI will then assign the participant to either the control or intervention group according to the concealed allocation contained within the envelope.

### Blinding

This is an open-label trial. Neither participants nor investigators are blinded due to the nature of the intervention.

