### Assessment and data collection

The principal investigator (PI) oversees all data management activities, including data entry verification, cleaning, codebook maintenance, and data security. Participants will undergo baseline and follow-up evaluations at 30, 60, and 90 days (end of treatment), as well as at 180 days (90-day follow-up). Specific assessments include visual acuity (LogMAR), VF testing (perimetry), OCT RNFL thickness, IOP, CCT, and laboratory investigations (CBC, ESR, FBS, KFT, LFT), as outlined in
Table 3. The overall schedule is detailed in
Figure 1 and
Table 4. Instruments such as the Humphrey Field Analyzer and OCT are recognized as valid and reliable for glaucoma diagnostics. All personnel responsible for VF tests, OCT scans, or tonometry received protocol-specific training. CRFs and compliance charts are securely stored at the coordinating center, and standardized operating procedures (SOPs) are employed throughout the data entry process to maintain consistency and accuracy.

**Table 3. T3:** Details of parameter assessment.

S. No	Parameters		Unit	Instrument
1.	Visual acuity - Distant		Number in decimals	ETDRS LogMAR chart
				Landolt C LogMAR chart
				Tumbling E LogMAR chart
2.	Visual acuity - Near		Number in decimals	ETDRS LogMAR near vision chart
3.	Best corrected visual acuity		Number in decimals	ETDRS LogMAR chart
4.	Perimetry	GHT	Outside normal limits-1 Within normal limits-0	ZEISS Humphrey field analyser 3 (HFA), Mark III SITA standard 30–2
		VFI24-2	In %	
		MD30-2	dB	
		PSD30-2	dB	
5.	OCT- OPTIC DISC CUBE 200x200	Average RNFL Thickness	μm	ZEISS CIRRUS HD - Optical Coherence Tomography (OCT)
		RNFL Symmetry	%	
		Rim Area	mm ^2^	
		Disc Area	mm ^2^	
		Average C/D Ratio	Number in decimals	
		Vertical C/D Ratio	Number in decimals	
		Cup Volume	mm ^3^	
6.	IOP measurement		mm of Hg	Goldmann Applanation tonometer, TOPCON Non-Contact Tonometer (NCT), Adjusted value
7.	Central corneal thickness (CCT)		mm	TOPCON Pachymeter/ZEISS CIRRUS HD - OCT

CCT – central corneal thickness, C/D Ratio – cup-to-disc ratio, ETDRS – early treatment diabetic retinopathy study, GHT – glaucoma hemifield test, IOP – intraocular pressure, LogMAR – logarithm of the minimum angle of resolution, MD – mean deviation, NCT – non-contact tonometer, OCT – optical coherence tomography, PSD – pattern standard deviation, RNFL – retinal nerve fiber layer, VFI – visual field index.

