### Data management

Data entry is conducted by PI using verification procedures, with all information recorded in a password-protected electronic database. Each participant is assigned a unique study ID, and direct identifiers are stored separately from the clinical dataset. The electronic database is accessible only to authorized personnel, and all physical documents (CRFs) are kept in locked cabinets at the study site. To ensure data quality, built-in range checks and validation rules automatically flag any out-of-range or inconsistent entries (Microsoft® Excel® for Microsoft 365 MSO (Version 2503 Build 16.0.18623.20076) 64-bit).

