### Confidentiality and data protection

Personal identifiers, such as names and addresses, are stored separately from the main clinical dataset to protect participant confidentiality. Any sharing of de-identified data with co-investigators or regulatory bodies will occur under secure data-transfer protocols. Physical copies of CRFs will be locked in secure cabinets, while digital records and databases will be password-protected. All study documents and electronic files will be retained for at least five years post-publication. Access to the de-identified final dataset will be restricted to the PI, co-PI, and the statistics team. No contractual agreement exists that would limit the research team’s right to publish or disseminate findings.

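### The reason given for open-label treatment does not cover outcome assessment or analysis, where no masking is stated, and the PI who assigns arms also enters the data

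*Protocol article*

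**What the plan says.** All references are to the protocol article.

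- **Blinding** calls the trial open-label and gives one reason: "Neither participants nor investigators are blinded due to the nature of the intervention". It names participants and investigators. It does not mention test operators or statisticians.
- **Randomization**: once eligibility is confirmed and enrolment recorded, the sealed envelope is opened. "The PI will then assign the participant to either the control or intervention group according to the concealed allocation contained within the envelope".
- **Data management**: "Data entry is conducted by PI using verification procedures, with all information recorded in a password-protected electronic database". Automatic range and validation checks are also described.
- **Assessment and data collection**: the PI "oversees all data management activities, including data entry verification, cleaning, codebook maintenance, and data security". On the testers it says: "All personnel responsible for VF tests, OCT scans, or tonometry received protocol-specific training". It does not say whether they are separate from the investigators.
- **Confidentiality and data protection**: access to the final dataset is "restricted to the PI, co-PI, and the statistics team", so a statistics team is listed apart from the PI and co-PI.
- **Outcomes**: the primary outcome rests on MD, PSD, VFI and RNFL thickness, and the secondary outcome is IOP by tonometry. Table 3 lists Goldmann, non-contact and adjusted IOP values.

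**The concern.** An oral powder and added eye drops with no placebo make it impractical to hide the arm from participants and from those who prescribe and dispense. That argument stops there. A person reading a Goldmann tonometer, deciding whether a field must be repeated, or accepting an OCT scan does not need to know the arm, and neither does the analyst. The section offers one justification for the whole open-label decision, and nothing elsewhere sets up masked assessment.

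Three features make this matter:

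- The person who knows every allocation also types in the outcome data and supervises its cleaning.
- Strategies to improve adherence to protocols has used and unused products returned at the 30, 60 and 90 day visits. Table 4 places outcome tests at the same visits, and no order is stated. A tester could learn the arm simply by being present.
- Statistical methods leaves the choice between parametric and nonparametric tests, and whether to impute, to judgement once the data are seen.

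A systematic difference in how the two arms are measured cannot be separated from a treatment effect at the analysis stage.

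**Working it through.** **Roles and masking, set side by side**

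| Role | Who | Does the stated reason explain knowing the arm? | Masking stated? |
|---|---|---|---|
| Taking the products | Participant | Yes | Stated as unblinded |
| Treating and dispensing | Investigators | Yes | Stated as unblinded |
| Opening allocation | PI | Yes, as an investigator | Stated as unblinded |
| Data entry; oversight of cleaning | PI | No, these tasks do not need the arm | Unblinded, as the same person |
| Perimetry, OCT, tonometry | Trained personnel, relation to investigators not given | No | Silent |
| Analysis | Statistics team | No | Silent |

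**Where knowledge of the arm can act**

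- Goldmann IOP: read by the operator, so most exposed. Non-contact readings are less so, but Tables 3 and 4 list both devices.
- MD, PSD, VFI: computed by the analyser. Operators act through coaching and repeat-test decisions, participants through their own responses.
- RNFL: computed by the OCT device. The operator acts mainly through scan acceptance.

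**Scale for IOP (illustration)**

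The protocol gives no alpha, SD or bias size, so it has no figure to reproduce. From Sample size: 30 intervention and 20 control (20 + 30 = 50; 20/30 = 2/3, as stated). Assumed: two-sided 5% test, no true effect, SD of change 3 mmHg, and a systematic shift b of 0.5 to 1.0 mmHg between arms from unmasked reading.

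SE = 3 × √(1/20 + 1/30) = 3 × 0.2887 = 0.866 mmHg.

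Type I error = Φ(b/SE − 1.96) + Φ(−b/SE − 1.96).

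- b = 0.5: b/SE = 0.58, giving 0.089.
- b = 1.0: b/SE = 1.15, giving 0.211.

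The same formula with the shift in SD units (SE = 0.2887) shows the sensitivity to the assumptions:

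| Shift (SD units) | Type I error |
|---|---|
| 0 | 5.0% |
| 0.1 | 6.4% |
| 0.2 | 10.7% |
| 0.3 | 18.0% |
| 0.5 | 41.0% |

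A 0.5 mmHg shift is 0.1 SD if the SD is 5 mmHg, and a 1.0 mmHg shift is 0.5 SD if the SD is 2 mmHg. Over SDs of 2 to 5 mmHg and shifts of 0.5 to 1.0 mmHg, the error therefore runs from 6.4% to 41.0%.

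**The case against.** The trial is openly labelled exploratory and open-label, and the article is condensed. Several objections have force.

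- A reader might infer that blinding is waived for everyone. The text does not support that: Blinding names participants and investigators only and is silent on testers and statisticians. The supportable statement is that no masking is provided for them.
- A reader might infer that the PI cleans the data. The text says the PI oversees cleaning; only data entry is stated as the PI's own task. Verification steps and automatic checks exist too. They catch errors but mask nobody.
- A reader might take the testers to be a dedicated, independent team, so that masking costs nothing. The text says only that they were trained. At a single site they may be the unblinded investigators, and then masking would need other people.
- A reader might see a fault in allocation concealment. None is shown: a research advisor generated the sequence, and envelopes are opened after eligibility is confirmed.
- The primary measures come from devices, and the calculation covers only the secondary outcome. This stands. Masked operators also cannot remove bias that unblinded participants introduce through their own field responses.
- Coded arms for analysts could be set out in an analysis plan that is not shown. If so, that part needs only a cross-reference.

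What remains is that the one stated reason does not reach assessment or analysis, and that allocation knowledge and data entry sit with the same person.

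**Conclusion.** The point holds in this limited form. The nature of the intervention justifies open-label treatment. It does not justify unmasked outcome assessment or analysis, and no section provides masking for either. The combination of allocating, entering data and overseeing cleaning in one unmasked role adds to the exposure.

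The weight falls mainly on Goldmann IOP and on repeat-test and scan-acceptance decisions. It is lighter for automated RNFL values. The rise in type I error from 5% to about 9% to 21% applies to IOP alone and depends wholly on an assumed SD of 3 mmHg and an assumed shift of 0.5 to 1.0 mmHg. It shows what such a shift would do with 30 and 20 participants. It is not evidence that a shift of that size, or any shift, occurs in this trial, and it says nothing about the size of bias in the primary outcome.

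**What to change.** Amend Blinding to say that participants and treating investigators are unmasked, and that existing testing personnel who are not treating investigators are not told the allocation. In addition:

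1. At each visit, complete perimetry, OCT and tonometry before returned products and compliance charts are handled.
2. Enter MD, PSD, VFI and RNFL thickness directly from device output. A Goldmann reading depends on its reader, so for IOP the protection comes from the tester not knowing the arm.
3. Give the statistics team coded arms until the primary output is final.
4. If the testers are the unblinded investigators, say so in Blinding and add unmasked assessment to Limitations.

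The cost is a protocol amendment, a minor reordering of tasks within existing visits, and a coded arm variable. Where testers separate from the treating investigators already exist, no further staff or tests are needed; the protocol does not show whether they do. Recruitment is still under way, so later visits can benefit, but those already completed cannot. Some accidental unmasking by participants will remain.

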### Criteria for discontinuing or modifying allocated interventions

If a participant experiences serious adverse events or shows clinically significant deterioration that appears linked to the RF or SP eye drops, the intervention may be paused or discontinued at the investigator’s discretion. Participants retain the right to withdraw voluntarily at any time. In cases where IOP or optic nerve parameters substantially worsen, or if an alternative therapy becomes necessary for emergent ophthalmic conditions, the intervention may also be modified or halted. If a participant becomes pregnant during the study, the intervention will be discontinued due to insufficient safety data in this population. All such modifications and discontinuations will be recorded in the case report forms (CRFs).

### Strategies to improve adherence to protocols

Participants will receive a compliance chart (see extended data) to track their daily intake of the RF and eye-drop usage. At each scheduled visit (30, 60, and 90 days), they will be required to return any empty or unused medication and eye-drop bottles, which will be counted to assess adherence. Regular check-ins via phone calls will be conducted to remind participants of follow-up appointments and dosing schedules (see extended data). During the baseline visit, each participant will be counseled on the importance of adherence, correct eye-drop instillation technique, and the potential benefits of completing the full intervention.

### Concomitant care and interventions

Participants will continue using standard anti-glaucoma medications, such as beta-blockers, prostaglandin analogs, or carbonic anhydrase inhibitors, as prescribed by treating ophthalmologists, unless contraindicated. Introduction of any new Ayurvedic formulation with overlapping ingredients or additional investigational drugs will be prohibited. Additionally, participants will be advised to maintain consistent dietary and lifestyle habits throughout the trial and to refrain from using any unauthorized herbal or nutraceutical supplements.

### Strategies for achieving adequate participant enrollment

A dedicated screening process for POAG is conducted at the Eye OPD, [name], AIIA, focusing on patients over 30 years of age. Outreach efforts include distributing pamphlets on glaucoma and Ayurveda-based management to both visitors and patients at the institute. Additionally, flexible scheduling options, including six-day-a-week or after-hours appointments, are offered to accommodate working participants and increase enrollment.

### Plans to promote participant retention

Participants receive reminder phone calls and messages a week and a day before each scheduled follow-up visit. Those with scheduling conflicts are offered alternative appointment times to ensure flexibility. In cases where participants discontinue the intervention, the study team attempts to conduct outcome assessments such as measuring IOP, performing optical coherence tomography (OCT), and conducting VF tests to capture essential end-of-study
data.

### Assessment and data collection

The principal investigator (PI) oversees all data management activities, including data entry verification, cleaning, codebook maintenance, and data security. Participants will undergo baseline and follow-up evaluations at 30, 60, and 90 days (end of treatment), as well as at 180 days (90-day follow-up). Specific assessments include visual acuity (LogMAR), VF testing (perimetry), OCT RNFL thickness, IOP, CCT, and laboratory investigations (CBC, ESR, FBS, KFT, LFT), as outlined in
Table 3. The overall schedule is detailed in
Figure 1 and
Table 4. Instruments such as the Humphrey Field Analyzer and OCT are recognized as valid and reliable for glaucoma diagnostics. All personnel responsible for VF tests, OCT scans, or tonometry received protocol-specific training. CRFs and compliance charts are securely stored at the coordinating center, and standardized operating procedures (SOPs) are employed throughout the data entry process to maintain consistency and accuracy.

**Table 3. T3:** Details of parameter assessment.

S. No	Parameters		Unit	Instrument
1.	Visual acuity - Distant		Number in decimals	ETDRS LogMAR chart
				Landolt C LogMAR chart
				Tumbling E LogMAR chart
2.	Visual acuity - Near		Number in decimals	ETDRS LogMAR near vision chart
3.	Best corrected visual acuity		Number in decimals	ETDRS LogMAR chart
4.	Perimetry	GHT	Outside normal limits-1 Within normal limits-0	ZEISS Humphrey field analyser 3 (HFA), Mark III SITA standard 30–2
		VFI24-2	In %	
		MD30-2	dB	
		PSD30-2	dB	
5.	OCT- OPTIC DISC CUBE 200x200	Average RNFL Thickness	μm	ZEISS CIRRUS HD - Optical Coherence Tomography (OCT)
		RNFL Symmetry	%	
		Rim Area	mm ^2^	
		Disc Area	mm ^2^	
		Average C/D Ratio	Number in decimals	
		Vertical C/D Ratio	Number in decimals	
		Cup Volume	mm ^3^	
6.	IOP measurement		mm of Hg	Goldmann Applanation tonometer, TOPCON Non-Contact Tonometer (NCT), Adjusted value
7.	Central corneal thickness (CCT)		mm	TOPCON Pachymeter/ZEISS CIRRUS HD - OCT

CCT – central corneal thickness, C/D Ratio – cup-to-disc ratio, ETDRS – early treatment diabetic retinopathy study, GHT – glaucoma hemifield test, IOP – intraocular pressure, LogMAR – logarithm of the minimum angle of resolution, MD – mean deviation, NCT – non-contact tonometer, OCT – optical coherence tomography, PSD – pattern standard deviation, RNFL – retinal nerve fiber layer, VFI – visual field index.

